### Data Analysis

Data analysis for this study will integrate both quantitative and qualitative approaches to provide a comprehensive understanding of AGYW engagement with LAI-PrEP and LARC. Quantitative data collection will involve administering structured questionnaires designed to capture preferences, attitudes, and perceptions regarding LAI-PrEP and LARC. The questionnaires will include Likert scale items to assess levels of agreement or disagreement with statements on acceptability, interest, and intent to use these interventions, alongside questions addressing barriers and facilitators to uptake. Additional sections will gather demographic information, reproductive health history, and HIV prevention behaviors. All data will be entered into REDCap [56] and exported to Stata for analysis. Analysis will begin with descriptive statistics to summarize participant characteristics and key variables, including acceptability, likelihood to recommend, and behavioral readiness. Frequencies, percentages, means, medians, standard deviations, and interquartile ranges will be reported to describe categorical and continuous data. Inferential analyses will then be conducted to identify associations and predictors. Correlations using Pearson or Spearman tests will examine relationships between continuous variables, such as age, education level, and preferences for LARC and LAI-PrEP. Likert scale responses will be collapsed into dichotomous outcomes (eg, agree vs disagree) and analyzed using chi-square tests to evaluate associations with demographic or behavioral factors.

Logistic regression models will be used to identify predictors of high acceptability and willingness to use integrated LARC and LAI-PrEP services. Variables considered clinically or theoretically relevant, together with those demonstrating an association at the bivariate analysis stage (*P*<.20), will be considered for inclusion in the multivariable models. Potential confounders, including age, education, socioeconomic status, marital status, prior contraceptive use, and HIV prevention history, will be retained in the final models where appropriate, based on subject-matter knowledge and statistical significance. Multicollinearity among independent variables will be assessed using variance inflation factors (VIFs) and correlation matrices. Where scientifically justified, interaction effects (for example, between age group and prior contraceptive use) will be explored by including interaction terms in the regression models. Model fit and assumptions will be evaluated using appropriate diagnostic procedures, including goodness-of-fit tests and assessment of influential observations. Adjusted odds ratios (aORs) with 95% CIs will be reported, and statistical significance will be assessed at a 2-sided α level of .05. Comparative analyses using 2-tailed *t* tests or ANOVA will further explore differences in preferences and attitudes across subgroups, including younger (15-19 years) versus older (20-24 years) AGYW and rural versus urban participants. For clarity of interpretation, results will be presented in tables summarizing numerical data and key statistics, including odds ratios (ORs) and *P* values. They will be visually illustrated with bar charts, pie charts, and histograms. Clustered bar charts and box plots will be used to highlight subgroup differences and significant predictors. This combined descriptive, inferential, and visualization approach will provide a robust understanding of AGYW preferences and attitudes toward LARC and LAI-PrEP, identify key facilitators and barriers to their uptake, and reveal demographic and behavioral predictors of positive engagement with these prevention methods.

Qualitative data from FGDs and IDIs will be audio-recorded, transcribed verbatim, translated into English where necessary, and analyzed using reflexive thematic analysis following Braun and Clarke's six-phase approach: (1) familiarization with the data, (2) generating initial codes, (3) constructing themes, (4) reviewing and refining themes, (5) defining and naming themes, and (6) producing the final report [57,58]. Codes will be developed inductively from the data while being interpreted in relation to the study objectives and the COM-B model. The multidisciplinary research team will engage in reflexive discussions throughout the analytical process to consider how their disciplinary backgrounds, experiences, and assumptions may influence data interpretation. An audit trail documenting coding decisions, codebook development, and theme refinement will be maintained throughout the analysis. Credibility will be enhanced through investigator triangulation, with different researchers independently reviewing transcripts and discussing emerging themes to reach consensus. Dependability and confirmability will be strengthened through regular analytical meetings and documentation of methodological decisions, while transferability will be supported by providing rich descriptions of the study setting, participants, and context. To support systematic analysis, NVivo software (Lumivero) will be used to organize transcripts, codes, and categories, while advanced query tools will facilitate the identification of thematic connections and overlaps. Quality assurance will be maintained through double coding of transcripts by 2 independent analysts, with discrepancies resolved through consensus discussions and peer debriefs to enhance validity. Once themes are consolidated, barriers to LARC and LAI-PrEP uptake will be mapped onto the COM-B model, categorizing them into domains of capability, opportunity, and motivation. This mapping will provide a structured behavioral lens through which challenges can be understood. Finally, insights from this process will guide the study team in collaboration with a behavioral science expert and key stakeholders to develop behavior change strategies informed by the BCW, ensuring that the interventions proposed are evidence-based, contextually appropriate, and designed to support AGYW in adopting and sustaining use of LARC and LAI-PrEP services. Following separate quantitative and qualitative analyses, findings from both components will be integrated using a convergent mixed methods approach. Integration will occur during the interpretation phase through triangulation to identify areas of convergence, complementarity, and divergence across data sources. Quantitative and qualitative findings will be merged using data mapping techniques (eg, joint displays) to identify connections and compare and contrast findings [59,60]. This approach will provide a comprehensive understanding of the behavioral, social, and health system factors influencing the uptake and implementation of integrated LARC and LAI-PrEP services.

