### Sample Size and Sampling Procedures

The quantitative sample size of up to 220 AGYW was estimated using the Kish-Leslie formula [51], assuming an 85% acceptability of LARC and LAI-PrEP if these services were made available. This sample size enables robust estimation of preferences, attitudes, and willingness to use integrated services, while accounting for variability in uptake across the study population. Participants will be purposively selected from the three KCCA clinics to ensure representation across urban, suburban, and peri-urban settings. For FGDs, a subset of 30 AGYW who completed the quantitative survey will be selected using stratified purposive sampling to ensure diversity in age, LARC and PrEP experience, and socio-demographic characteristics. This approach will enable in-depth exploration of factors influencing uptake and adherence. KIs will also be purposively sampled to capture a wide range of perspectives, professional roles, and influence over reproductive health and HIV prevention services. This combined sampling approach ensures a comprehensive understanding of both individual-level experiences and community-level factors affecting the integration and uptake of LARC and LAI-PrEP among AGYW in Uganda.

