## Results

The study was funded in February 2026. Ethical and regulatory approvals were obtained before study initiation. Study preparation, including site initiation, staff training, finalization of study instruments, and community sensitization, was completed before participant recruitment. Participant recruitment began in March 2026 and was completed in July 2026, at selected KCCA clinics and community settings. A total of 220 AGYW and 20 KIs were enrolled, and both quantitative and qualitative data collection were completed in July 2026. Data cleaning and quality assurance activities were ongoing, and quantitative and qualitative data analyses were planned following completion of data collection. No major protocol modifications have been made since study initiation. Study findings are anticipated to be submitted for publication in 2027, following completion of data analysis and manuscript preparation.

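### If willingness is near the 85% planning value, its regression rests on about 33 not-willing women, so ordinary logistic fits would moderately overstate odds ratios; a Firth fit and an exploratory label would deal with this

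*Protocol article*

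**What the plan says.** All references are to the protocol article.

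- **Sample Size and Sampling Procedures** derives a maximum of 220 from the Kish-Leslie single-proportion formula, "assuming an 85% acceptability of LARC and LAI-PrEP if these services were made available". It adds: "This sample size enables robust estimation of preferences, attitudes, and willingness to use integrated services". It gives no margin of error, non-response allowance, effect size, power or number of model parameters.
- **Data Analysis** applies regression to the same women: "Logistic regression models will be used to identify predictors of high acceptability and willingness to use integrated LARC and LAI-PrEP services". On covariates: "Potential confounders, including age, education, socioeconomic status, marital status, prior contraceptive use, and HIV prevention history, will be retained". That sentence then makes retention conditional on appropriateness, judged from subject-matter knowledge and statistical significance. Theory-based variables and those passing a bivariate screen at P<.20 are also candidates. Given a scientific case, "interaction effects (for example, between age group and prior contraceptive use) will be explored by including interaction terms in the regression models". The listed checks are variance inflation factors, correlation matrices, goodness of fit and influential observations. No penalised or exact method is named.
- **Data Collection** splits the composite acceptability score at its observed median for descriptive purposes. **Data Analysis** collapses Likert items into two classes, with agree versus disagree as the example.
- **Results** reports that "A total of 220 AGYW and 20 KIs were enrolled" and that analysis had yet to start.

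**The concern.** In a binary regression the information is limited by the rarer outcome class, not by the total sample. A sample that is adequate for one proportion near 85% leaves few women in the other 15%. With a handful of them per coefficient, maximum-likelihood odds ratios are pushed away from 1, and a small covariate category can contain no not-willing women at all, so that its coefficient has no finite estimate. The diagnostics listed in Data Analysis correct neither problem, and both arise even when the covariates are fixed in advance.

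At stake is how far the adjusted odds ratios for willingness can be trusted when they are tabulated, charted as significant predictors and merged with the qualitative findings. Recruitment has closed, so only the estimator, the model size and the wording of the claim can still change.

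**Working it through.** **1. The plan's own figure.** Formula: n = z²p(1−p)/d², with p = 0.85 (stated) and z = 1.96. The margin d is not stated.
- With d = 0.05 assumed: 3.8416 × 0.1275 / 0.0025 = 195.9, so 196. With 10% non-response assumed: 196/0.9 = 218.
- With d = 0.047 assumed and no inflation: 222.

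Either route lands close to 220, so the figure is reproducible as a single-proportion size. At n = 220 the half-width is 1.96 × √(0.85 × 0.15/220) = 0.047, or 4.7 points.

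**2. The smaller class.** Count = 220 × (1 − willing proportion). Six terms means one per named confounder. Nine means two each for education, socioeconomic status and marital status, which assumes three levels apiece.

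| Willing (assumed) | Not willing | Per coefficient, 6 terms | Per coefficient, 9 terms |
|---|---|---|---|
| 75% | 55 | 9.2 | 6.1 |
| 80% | 44 | 7.3 | 4.9 |
| 85% | 33 | 5.5 | 3.7 |
| 90% | 22 | 3.7 | 2.4 |
| 95% | 11 | 1.8 | 1.2 |

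The ratio is below 10 throughout.

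**3. Effect on the estimates.** Simulated surveys of 220 women, true OR 2 for the predictors assessed. Covariate prevalences are assumptions. Maximum-likelihood averages leave out separated fits.

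| Setting | Mean excess in log OR | Datasets with separation |
|---|---|---|
| 85%, nine terms, 2,000 datasets | 5-13% | 9% |
| 85%, six / eight / ten binary terms, 1,000 datasets each | 5% / 9% / 12% | 5-6% |
| 90%, nine terms | 6-14% | 22% |
| 85%, nine terms plus two interactions | 10-17% | 27% |
| 50:50 outcome, six to fifteen binary terms | 3-7% | 0% |

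A further simulation with six to nine terms and other covariate assumptions gave an excess of about 4-13% at 85%. Separation there was under 1% to 3% at 85% and 2-11% at 90%. The size of the bias is therefore stable across set-ups, while the separation rate depends heavily on how sparse the covariate categories are.

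Firth fits of the same data had mean log ORs within about 5% of the truth, and root mean squared error about 6-11% lower.

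**4. Bias against noise.** An excess of 5-13% turns a true OR of 2 into 2^1.05 = 2.07 to 2^1.13 = 2.19. Power in the nine-term simulation was 28-42%. Since power = Φ(ln 2/SE − 1.96), this implies SE of about 0.50 to 0.39. The bias is 0.05 × 0.693 = 0.035 to 0.13 × 0.693 = 0.090, roughly 0.1 to 0.2 of a standard error. At SE 0.39, a 95% CI around OR 2 runs from about 0.9 to 4.3. CI coverage in the simulations was near nominal. Imprecision is thus the larger limitation, and bias the smaller one.

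**The case against.** **The 33 is not a protocol figure for willingness.** The 85% is labelled acceptability, and the primary acceptability score is cut at its median. This stands, so the count is given as a range. Eligibility requires LARC use or existing interest, which makes a rate above 85% plausible, but the documents do not settle it.

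**No parameter count is fixed.** Confounders may be dropped and interactions are conditional. The nine terms and two interactions are assumptions made here; the protocol names one interaction, as an example. This stands, and it is why the result is stated for six to nine terms.

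**The bias is small and part of it is general.** Also correct: even a balanced outcome shows a 3-7% excess, and coverage holds.

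**The estimator belongs in an analysis plan that is not shown.** Maximum likelihood is indeed inferred from an unqualified reference to logistic regression. However, the article does set out the model, covariates, interactions and diagnostics, and naming a better-suited fit for sparse outcomes improves on that stated method.

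A reader might infer more, without support in the documents:
- *That the robustness sentence is false.* It speaks of estimating preferences, attitudes and willingness, and makes no claim about regression.
- *That separation will be common.* At 85% it is occasional.
- *That faulty odds ratios drive the behavior change strategies directly.* Table 2 draws both the barriers and facilitators and the strategies from focus groups and interviews. The survey results enter by triangulation, although Data Analysis does expect them to help identify facilitators and barriers.

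**Conclusion.** The point holds at moderate size. The sample was sized for one proportion, and the willingness regression probably has far fewer informative women than 220 suggests. At 85% that means about 33, or roughly 4 to 5.5 per coefficient with six to nine terms. Ordinary logistic regression would then overstate log odds ratios by about 5-13% on average, with separation in up to about 9% of datasets, rising at 90% or with interactions.

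This rests on three assumptions: willingness near the only planning value given, a maximum-likelihood fit, and the covariate distributions used in the simulations. If high acceptability means the median split and ties at the median are few, that model has roughly 110 women per class and is outside the problem. The finding does not show that 220 is the wrong number for its stated purpose, nor that the planned confidence intervals would be invalid.

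**What to change.** **In Data Analysis**, state that the willingness model, and any other binary outcome whose smaller class gives fewer than about 10 women per coefficient, will be fitted by Firth penalised-likelihood logistic regression with profile-penalised 95% CIs. Set the number of terms in advance from the observed smaller-class count, which can be tabulated without looking at any predictor. With 33 women, 10 per coefficient would allow only three terms (33/10 = 3.3), so a penalised fit is more practical than cutting the model to reach that ratio. Report the resulting odds ratios as exploratory: Firth removes most of the bias but does not restore power.

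**In Sample Size and Sampling Procedures**, add that 220 was sized for the overall proportion and not for the predictor models.

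There is no need to confine the model to the six named confounders, impose ordinal scores or rule out interactions. Those restrictions could remove the very predictors the analysis seeks.

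**Cost:** a few sentences and a user-written Stata command, with no new data. The downsides are slightly shrunken odds ratios and a less favourable statement of what 220 supports.

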
### Ethical Considerations

The study received ethical approval from the Joint Clinical Research Centre (JCRC-REC 2025-143). Administrative clearance was obtained from the KCCA (DPHE/KCCA/1302/01) and approval from the Uganda National Council for Science and Technology (HS6232ES). All participants will provide written informed consent before any study procedures are carried out. Consent is viewed as an ongoing process conducted through open dialogue between study staff and participants. For AGYW, the screening and enrolment consent also includes embedded consent for possible participation in FGDs, eliminating the need for additional signatures. KIs similarly provide informed consent for enrolment and participation in IDIs at the screening and enrolment visit. Minors under 18 years may participate in the study. The JCRC-REC granted a waiver of parental consent because the study posed less than minimal risk. Consenting staff will follow Makerere University–Johns Hopkins University Research Collaboration’s (MU-JHU’s) Standard Operating Procedures using institutional review board (IRB)–approved forms in both English and Luganda, which are color-coded by participant group. Comprehension will be evaluated with an assessment of understanding tool, enrolling only those who demonstrate sufficient understanding and consent voluntarily. Additional safeguards will be implemented for participants aged 15-17 years to ensure their safety and well-being throughout the study. Interviews and FGDs will be conducted in private settings to protect confidentiality and encourage open discussion of sensitive topics. Participants will be reminded that participation is voluntary and that they may decline to answer any question, pause, or withdraw from the study at any time without penalty or loss of services. Study staff will be trained to recognize and respond appropriately to signs of distress. Participants requiring additional support will be referred to appropriate psychosocial, counseling, or clinical services in accordance with established referral procedures. All study personnel will receive training in Human Subjects Protection and Good Clinical Practice. The study will ensure confidentiality by removing participant identifiers from data, locking name-ID logs and signed consents in secure locations, and storing electronic data on password-protected computers. Participant rights, including the right to withdraw voluntarily, will be upheld. The study is classified as minimal risk but may cause discomfort or anxiety when answering sensitive questions related to reproductive health or HIV prevention. Although measures are in place to safeguard information, there remains a minor risk of unintended disclosure that could lead to social harm or stigma. Trained study staff will offer support for any concerns participants may have.

Participants in this study will not receive direct benefits; however, their involvement will help improve access to and acceptance of integrated LARC and LAI-PrEP services for AGYW in Uganda. The study allows participants to voice their opinions and help shape the design of more responsive and inclusive reproductive health and HIV prevention programs. Findings will be shared according to Uganda National Council for Science and Technology (UNCST) policies [61], prioritizing transparency and equity in dissemination to relevant audiences. Preliminary findings will be submitted to the local research ethics committees prior to any public release. The study results will be shared with study participants and community representatives via dissemination meetings at study sites, using culturally appropriate methods aligned with Good Participatory Practice principles [62] to ensure understanding and interaction. After local dissemination, findings will be presented to stakeholders, including KCCA health officials and partners. The study team will create policy briefs highlighting key findings and recommendations for the integrated delivery of LARC and LAI-PrEP among AGYW in Uganda. Nationally, results will also be shared with the Uganda Ministry of Health and relevant agencies through technical working groups, workshops, and dialogues. Additionally, findings will be presented to the scientific community at conferences and in peer-reviewed publications.

## Results

The study was funded in February 2026. Ethical and regulatory approvals were obtained before study initiation. Study preparation, including site initiation, staff training, finalization of study instruments, and community sensitization, was completed before participant recruitment. Participant recruitment began in March 2026 and was completed in July 2026, at selected KCCA clinics and community settings. A total of 220 AGYW and 20 KIs were enrolled, and both quantitative and qualitative data collection were completed in July 2026. Data cleaning and quality assurance activities were ongoing, and quantitative and qualitative data analyses were planned following completion of data collection. No major protocol modifications have been made since study initiation. Study findings are anticipated to be submitted for publication in 2027, following completion of data analysis and manuscript preparation.

## Discussion

### Anticipated Findings

This mixed methods cross-sectional implementation science study addresses a global health priority in HIV prevention and reproductive health programming by exploring the integration of two long-acting biomedical interventions, LARC and LAI-PrEP, for AGYW in Uganda. While both interventions have demonstrated high efficacy and acceptability, their integration within routine service delivery remains limited, and evidence on how best to deliver them jointly to meet the needs of AGYW is scarce. The introduction of lenacapavir and other long-acting prevention agents further underscores the need to design context-appropriate models that support combination prevention options [63,64]. COMPASS responds to this need by generating behavioral and implementation evidence to guide integrated service delivery in real-world settings.

A key strength of this protocol lies in its deliberate approach to intervention design. Too often, biomedical innovations are introduced without sufficient consideration of behavioral, social, and contextual factors that shape adoption and sustained use [65]. Prior studies have shown that interventions grounded in these frameworks are more likely to be effective and feasible, particularly in HIV prevention and reproductive health settings [66-70]. By integrating theoretical frameworks, COMPASS systematically identifies determinants of behavior and guides the development of tailored, theory-driven strategies. Being intentional in this design process ensures that emerging interventions are not only evidence-based but also relevant, feasible, and scalable within the Ugandan health system. Such deliberateness in the early design stages is particularly valuable, given the rapid evolution of long-acting HIV prevention technologies and the ongoing need to align service models with end-user preferences and health system realities.

The study’s participatory and co-design components further strengthen its methodological rigor. By engaging AGYW, peers, and health care providers throughout, the study captures diverse perspectives and enhances ownership of proposed solutions. COMPASS is also designed to empower AGYW, promoting autonomy, informed decision-making, and self-efficacy. Previous studies have shown that co-designing tools and interventions with end-users has been shown to improve the acceptability, feasibility, and sustainability of HIV prevention and reproductive health interventions among young populations [69,71,72]. The mixed methods design, which integrates quantitative surveys, qualitative interviews, and participatory co-design activities, allows triangulation of findings, providing a rich and tailored understanding of the social, behavioral, and structural factors that influence uptake of integrated LARC and LAI-PrEP services. This approach is expected to yield actionable strategies that can be tested in future implementation trials or scaled within existing programs.

We also recognized some limitations. The study’s focus on urban, suburban, and periurban settings in Kampala may limit the transferability of findings to rural areas, where health system capacity, cultural norms, and service delivery models may differ. Nevertheless, the inclusion of urban, peri-urban, and suburban clinics serving diverse populations provides evidence that is likely to be applicable to similar service delivery settings elsewhere in Uganda and in other sub-Saharan African countries facing comparable HIV and reproductive health challenges among AGYW. Rather than aiming for external validity, this implementation science study seeks to generate relevant evidence that can inform the adaptation of integrated LARC and LAI-PrEP delivery strategies. Future implementation in rural settings should consider differences in health system capacity, access to youth-friendly services, cultural norms, and community engagement approaches when adapting the proposed strategies.

Participant recruitment may also be subject to selection bias because clinic-based recruitment may preferentially enroll AGYW who are already engaged with health services, while peer-led snowball sampling may overrepresent individuals within existing social networks. To reduce this potential bias, the study incorporates community-based recruitment through peer networks, community health workers, community sensitization activities, and outreach beyond clinic settings, in addition to recruitment across three KCCA clinics that serve different populations: Kisenyi (urban), Kawaala (peri-urban), and Komamboga (suburban). Although these approaches are intended to broaden participant representation, some residual selection bias may remain.

Additionally, reliance on self-reported measures regarding sexual behavior, contraceptive use, and PrEP adherence may be affected by recall and social desirability bias [73-75]. Mitigation strategies, including confidential data collection methods and triangulation across multiple data sources, are built into the design to reduce these risks. Nonetheless, these limitations provide opportunities for future work, including follow-up studies to assess the applicability of identified strategies in rural contexts and longitudinal evaluations to determine their impact on sustained uptake and adherence. Future directions will also include pilot testing of co-designed interventions to refine their feasibility, cost-effectiveness, and scalability across diverse service delivery settings.

The evolving global HIV prevention funding and policy landscape further reinforces the significance of this research. Recent reductions and policy shifts in funding for the President’s Emergency Plan for AIDS Relief (PEPFAR) and the United States Agency for International Development (USAID) have heightened the emphasis on cost-efficiency, sustainability, and local ownership in HIV programming [76,77]. Although this study is not expected to be directly affected by these funding shifts, its focus on community-driven and contextually relevant implementation approaches aligns with global priorities to optimize resources and strengthen health systems.

In this environment, implementation science research becomes even more critical, as it provides evidence to guide the integration of new biomedical tools into existing infrastructure. Simultaneously, the increasing global enthusiasm for long-acting prevention agents, such as lenacapavir, highlighted by regulatory approvals and global guidelines, underscores the timeliness of COMPASS. The study’s findings will contribute practical evidence on how future long-acting products can be delivered effectively and equitably, particularly for AGYW who remain at elevated risk but are often underserved in current programs.

